## Assignment of interventions: blinding

This is a triple-blind study, where neither the investigator responsible for the intervention nor the patients included in the study will know at any time whether they receive Alantel cream or control moisturizing cream. The statistician in charge of the analysis will also remain blind. The product bottles will be similar in appearance, containing the active substances for the EG and a harmless moisturizing substance for the CG. The company making the Alantel cream will also prepare and provide the moisturizing cream.

## Data collection and management

The person in charge of monitoring the fieldwork of the study will contact the field researchers, if necessary, to complete the missing data in the data collection forms under the supervision of the principal investigator, who will not participate in the collection and mechanization of the data. After the trial, patients’ personally identifiable information will be removed and placed in a separate database for statistical analysis. The database that will be generated to process data from the case report form (CRF) will not collect any patient identification or demographic data. Each patient will be identified with an alphanumeric code, so the methodologist in charge of statistical analysis will be unaware of the patients’ identities. Only the members of the study management team (the principal investigator, the research oncologist in charge of the study in her Oncology department, the person in charge of the methodology), the research assistant in charge of data mechanization, and the person in charge of the Clinical Research and Ethics Committee who approved the trial will have access to the trial data set. The CRF will be safeguarded and kept in a place with appropriate security. Only individuals with permission granted by the principal investigator can access it.

The data collected in the CRF will be mechanized by a research assistant in a database created in Google Drive (Google Form tool). Only the principal investigator and the methodologist supervising the process and checking the data entered will have access, paying special attention to inconsistent data, outliers, and missing data.

The final data of the trial will be available to the project funder and the Ethics Committee. The personal information of the participants will be stored in a database that will be guarded by the principal investigator throughout the study period, safeguarding it for 5 years, as established by the Spanish legislation.

## Statistical methods

After the mechanization and filtering of the data, a descriptive analysis will be performed that will include the characteristics of the studied population (sociodemographic variables) and outcome variables using measures of central tendency, dispersion, and position in the quantitative variables and tabulation and calculation of relative frequencies in qualitative variables. The calculation of the main estimators with their corresponding confidence intervals for 95% safety will also be performed. An intention-to-treat analysis will be performed. To minimize the problem of missing data, the analysis will be performed by dragging the data from the visit from which they are obtained to the following visits and to the final one. That is, the intent-to-treat analysis will include all participants assessed at least once after randomization. In addition, a per-protocol analysis will be performed, defined as the group of participants who comply with the procedure to be followed, including the use of the substances tested in the study, in at least 80%. A pre-post-intervention comparative analysis will then be performed with the endpoints used; for this, we will use means comparison tests taking into account the results obtained in each of the visits (parametric, such as ANOVA for repeated measures, if the variables follow a normal distribution—Shapiro-Wilk Test—or non-parametric, such as Friedman’s test, if they do not follow it), or proportion comparison test on qualitative variables, such as Pearson’s chi-square test or Fisher’s exact test (*p* < 0.05). Finally, the results will be statistically compared between groups using the log-rank test after estimating the survival curve with the Kaplan-Meier method. Multiple linear regression analysis-dependent variable: results obtained with the VAS, and the survival analysis, by Cox regression-dependent variables: RD or no; RD improvement vs. no improvement and cured vs. non-cured will be performed to evaluate the effect of the product, adjusting for the sociodemographic and clinical variables presumably predictive or confounding. Statistical analysis will be performed using SPSS v.17.0 and EPIDAT 4.1 packages.

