#### Sample size

Taking as reference those values provided in a previous study [20], the expected occurrence rate of RD (primary outcome variable) would be 46.7% in EG and 78.6% in CG, respectively; with a 1:1 allocation, accepting an alpha risk of 0.05 (5%) and a beta risk of 0.20 (20%), and assuming a follow-up loss rate of 20%, 88 eligible patients (44 in each group) are needed (calculations performed with the Granmo software version 7.12 in: https://www.imim.cat/ofertadeserveis/softwarepublic/granmo/, sample size for two independent proportions).

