### Adverse event reporting and harms

Possible AE will be evaluated and reported during the study, and their causal relationship with the components of the cream will be assessed. If an AE is found, the researcher will evaluate the intensity and frequency of each episode and decide whether additional treatments are needed. These AE will be notified to the Andalusian Pharmacovigilance Center and the Ethics Committee of the Reina Sofia Hospital (Cordoba, Spain). If the physician considers it appropriate, the patient will be withdrawn from the study.

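### Carrying the last visit forward scores patients lost while free of RD as RD-free at the end, which understates incidence and matches neither the sample size nor the planned survival analyses

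*Protocol article*

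**What the plan says.** The primary outcome is the incidence of RD (Outcomes, Table 2). Skin is assessed after sessions 5, 10 and 15 and one week after radiotherapy ends (Interventions).

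Statistical methods fills missing visits by "dragging the data from the visit from which they are obtained to the following visits and to the final one". It then defines the population: "the intent-to-treat analysis will include all participants assessed at least once after randomization". The only other analysis set is per-protocol. The same paragraph plans Kaplan-Meier curves, a log-rank test and Cox regression. It does not say how a patient who is lost enters them.

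The Sample size section assumes that "the expected occurrence rate of RD (primary outcome variable) would be 46.7% in EG and 78.6% in CG" and concludes, "assuming a follow-up loss rate of 20%, 88 eligible patients (44 in each group) are needed".

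On leaving the trial, Adverse event reporting and harms says: "If the physician considers it appropriate, the patient will be withdrawn from the study". Interventions has the same rule, and Withdrawals or dropouts from the trial adds withdrawal on clinical criteria.

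**The concern.** RD is a cumulative event. Once recorded it stays recorded, and a patient without it remains at risk until the last visit. Carrying an RD-free status forward can therefore err in one direction only: it misses RD that appears after the patient is lost.

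- **Equal loss in the two arms.** Both incidences fall, the difference shrinks towards zero, and some power is lost.
- **Unequal loss.** The arm that loses more patients looks better, whether or not the cream works.

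The plan also treats the same lost patient in incompatible ways. The sample size removes her, the carry-forward rule gives her an outcome, and a survival analysis would ordinarily censor her. A physician may withdraw a patient from the study after an adverse event. A reaction to the cream and RD are both skin events, so such losses may be related to arm or outcome.

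**Working it through.** **Inputs from the protocol.** RD rates 46.7% and 78.6%; alpha 0.05, power 80%, 1:1 allocation, 20% loss, 44 per arm; four skin visits. Sidedness is not stated; two-sided is assumed, and it reproduces the stated size.

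**Inputs assumed.** How RD hazard is spread over the visits, and when patients are lost. The protocol gives neither.

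**1. The plan's own figure.** For two proportions with pooled variance and no continuity correction, the mean rate is (0.467 + 0.786)/2 = 0.6265.

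n = [1.96 × √(2 × 0.6265 × 0.3735) + 0.8416 × √(0.467 × 0.533 + 0.786 × 0.214)]² / 0.319² = (1.341 + 0.544)² / 0.1018 ≈ 34.9, so 35 per arm.

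35/0.80 = 43.75, so 44 per arm and 88 in total. The stated size reproduces. Dividing by 0.80 means that the lost patients contribute nothing and about 35 per arm are analysed at the undiluted rates (power 80.1%).

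**2. Carry-forward in closed form.** Let f be the share of the lost patients' eventual RD recorded before loss. With 20% loss, each rate p becomes p × (0.8 + 0.2f), now with 44 per arm analysed.

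| f | EG | CG | Difference (points) | Power |
|---|---|---|---|---|
| 0 | 37.4% | 62.9% | 25.5 | 67.3% |
| 0.25 | 39.7% | 66.8% | 27.1 | 73.0% |
| 0.5 | 42.0% | 70.7% | 28.7 | 78.5% |
| 0.75 | 44.4% | 74.7% | 30.3 | 83.7% |
| 1 | 46.7% | 78.6% | 31.9 | 88.5% |

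Power falls below 80% when f is under about 0.57.

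**3. A concrete visit pattern.** Split the cumulative hazard −ln(1 − p) as 10/25/35/30% over the four visits. Cumulative RD is then 6.1, 19.8, 35.6 and 46.7% in EG, and 14.3, 41.7, 66.0 and 78.6% in CG. Every lost patient is taken to have attended at least the first visit.

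- Loss spread evenly after visits 1, 2 and 3: mean RD recorded by the time of loss is 20.5% (EG) and 40.7% (CG). Carry-forward gives 0.8 × 46.7 + 0.2 × 20.5 = 41.5% and 0.8 × 78.6 + 0.2 × 40.7 = 71.0%.
- All loss straight after visit 1: 0.8 × 46.7 + 0.2 × 6.1 = 38.6% and 0.8 × 78.6 + 0.2 × 14.3 = 65.7%.

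Simulated power (20,000 trials per scenario, 44 per arm, chi-square test on carried-forward status):

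| 20% loss per arm | Carry-forward | Log-rank, censored at last attended visit |
|---|---|---|
| Spread over visits | about 80% | about 87% |
| All after visit 1 | about 71% | about 85% |

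**4. No true effect, unequal loss.** Take 78.6% in both arms and 30% vs 10% loss. With spread loss the carried-forward rates are 0.7 × 78.6 + 0.3 × 40.7 = 67.2% and 0.9 × 78.6 + 0.1 × 40.7 = 74.8%, a spurious difference of 7.6 points. With all loss after visit 1 they are 59.3% and 72.2%, or 12.9 points.

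| Loss | Type I error, spread | Type I error, all after visit 1 | Censored log-rank |
|---|---|---|---|
| 20% vs 10% | about 7% | about 11% | about 5% |
| 30% vs 10% | about 13% | about 26% | about 5% |

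The simulated loss does not depend on the patient's RD status, so the last column holds only for non-informative loss.

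**The case against.** **The planned power may survive.** This stands. Carry-forward keeps up to 44 per arm in the analysis, and with loss spread over visits that offsets the dilution: about 80%, as planned. The figure of about 71% needs every loss to follow the first visit. At 10% loss, even that pattern leaves about 81%. A reader might infer that the trial is underpowered or its sample size wrong. The documents support neither: the calculation reproduces, and the defect is that the missing-data rule does not match it.

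**The inflated type I error needs strongly unequal loss.** This stands too. Nothing in the protocol predicts 30% vs 10%, and both arms use similar-looking creams under blinding. With equal loss, type I error stays near 5%.

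**Censoring has its own assumption.** Correct. If loss depends on outcome, the censored log-rank test is biased as well, so the 5% cannot be credited to it unconditionally.

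**The log-rank test is already planned, and censoring rules may sit in an unseen SAP.** This stands in part. The article does not say that carried-forward values enter the survival analysis, and it does not make clear which test is primary: the abstract and sample size point to proportions, while Statistical methods compares groups by log-rank. But carry-forward is stated for the analysis as a whole and no censoring is mentioned, so the two need reconciling.

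**Losses are already being limited.** Follow-up in the oncology service is offered to those who cannot travel, reasons for loss are logged, and missing data are chased. These steps reduce loss, yet 20% is still planned for.

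**Restricting intention-to-treat to patients assessed at least once.** A reader might count this as a further serious flaw. It adds almost nothing here, because a patient with no post-baseline visit contributes nothing to a log-rank test either.

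**Conclusion.** The point holds as a conditional weakness that should be fixed. What does not depend on a particular loss pattern is the direction: RD incidence is understated whenever a patient lost while RD-free would later have developed RD. The size does depend on assumptions about hazard, timing of loss and balance between arms, none of which the protocol gives.

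Under the pattern used here, equal 20% loss costs about 7 to 14 percentage points of power against a censored log-rank test (80 vs 87%; 71 vs 85%). The bias is then towards no difference. A raised false-positive rate requires unequal loss: modest at 20% vs 10%, substantial at 30% vs 10%. It would be too strong to say that the 80% power is lost, or that a 26% false-positive rate is to be expected.

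**What to change.** In Statistical methods:

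- Drop carry-forward as the main rule for RD. Analyse time to first RD over the four visits, censored at the last attended visit, with the log-rank test already planned.
- Report the Kaplan-Meier risk difference at the final visit with its 95% CI.
- State that this assumes non-informative loss.
- Use a mixed model or multiple imputation for the VAS and Skindex-29.
- Keep carry-forward, if wanted, only as a labelled sensitivity analysis.

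In Interventions, Withdrawals or dropouts from the trial, and Adverse event reporting and harms, separate stopping the cream from leaving follow-up, so that skin visits already scheduled are kept unless consent is withdrawn. This takes no position on when the cream should be stopped.

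The cost is a few sentences, with no extra patients and no visits beyond those scheduled. Trial status says the study concluded in June 2023, so the follow-up wording cannot recover visits already missed. The analysis change needs only the visit data already collected.

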**Methods:**

Our protocol is an experimental, prospective, triple-blind, multicenter, controlled clinical trial with two parallel arms. The experimental group will be treated with Alantel, while the control group will receive another moisturizing cream. Radiotherapy oncology professionals will recruit a total of 88 patients (44 per comparison group) with breast cancer who will receive radiotherapy oncology treatment for 15 days, and they will be randomly allocated to the experimental or control group. Selected patients will be followed up for four visits by primary care physicians for up to 1 week after completion of radiotherapy. The main study variable will be the incidence rate of mild post-radiation dermatitis. An intention-to-treat analysis will be performed, applying a comparison test for independent means and proportions. A bivariate and multivariate analysis will also be developed to check the treatment effect, adjusting for predictive sociodemographic and clinical variables.

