## Trial design

The Alantel study is designed as a randomized, controlled, multicenter, superiority, triple-blind trial, with two parallel groups.

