#### Outcomes

All outcomes are described in detail in Table 2. The primary outcome is the incidence of RD.

**Table 2 Tab2:** Primary and secondary outcomes

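### The tests of means and proportions are framed as pre-post, and no between-arm test is named for Skindex-29 or toxicity grade

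*Protocol article*

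**What the plan says.** Trial design: "The Alantel study is designed as a randomized, controlled, multicenter, superiority, triple-blind trial, with two parallel groups". Outcomes: "The primary outcome is the incidence of RD". Toxicity grade (0 to 4), discomfort (VAS, 0 to 10) and Skindex-29 are secondary outcomes in Table 2. Secondary objective (b) asks for quality of life before and after treatment, compared between women who do and do not use the cream.

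Statistical methods then gives the tests in two steps.

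- Step one: "A pre-post-intervention comparative analysis will then be performed with the endpoints used". For this purpose it names, for quantitative variables, a test that is "parametric, such as ANOVA for repeated measures, if the variables follow a normal distribution" by Shapiro-Wilk, or otherwise a non-parametric one such as Friedman. For qualitative variables it names Pearson chi-square or Fisher. No arm factor, arm-by-visit term or paired test of proportions is mentioned.
- Step two, introduced as the final comparison between groups: log-rank after Kaplan-Meier, Cox regression (dermatitis, improvement, cure) and multiple linear regression (VAS only), adjusted for covariates.

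The abstract describes the analysis differently, as "applying a comparison test for independent means and proportions". The Sample size section uses two independent proportions: "the expected occurrence rate of RD (primary outcome variable) would be 46.7% in EG and 78.6% in CG".

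**The concern.** The randomised question is whether the cream does better than the control cream. A pre-post test asks whether values move over time, and under radiotherapy skin scores can be expected to move in both arms. If step one is followed as written, three things go wrong.

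1. A score that fails Shapiro-Wilk goes to Friedman, which has no arm term. Skindex-29 and toxicity grade do not appear among the step-two methods, so nothing between arms is named for them.
2. Chi-square and Fisher assume independent samples. Applied to earlier and later values of the same patients, they ignore the pairing.
3. For dermatitis itself a pre-post test is uninformative. Patients with dermal lesions are excluded, and Table 1 records dermatitis only from the first follow-up visit, so the starting value is essentially zero in both arms.

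At stake is objective (b), and toxicity grade as a graded outcome: both could be reported through within-arm p-values that mainly reflect the course of radiotherapy.

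**Working it through.** **Which test covers which outcome, on the text of Statistical methods**

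| Outcome | Pre-post step | Between-arm method named |
|---|---|---|
| Dermatitis incidence | chi-square/Fisher | log-rank, Cox |
| Improvement, cure | chi-square/Fisher | Cox |
| VAS | RM-ANOVA or Friedman | linear regression |
| Skindex-29 | RM-ANOVA or Friedman | none |
| Toxicity grade | Friedman if treated as a score, chi-square/Fisher if as categories | none |

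**The plan's sample size is a between-arm calculation.** Inputs from the Sample size section: 0.467 and 0.786, alpha 0.05 (taken as two-sided; the section does not say), power 0.80, 20% loss. The mean rate is (0.467 + 0.786)/2 = 0.6265.

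- n per arm = [1.960 × √(2 × 0.6265 × 0.3735) + 0.8416 × √(0.467 × 0.533 + 0.786 × 0.214)]² / (0.786 − 0.467)²
- = (1.3408 + 0.5436)² / 0.10176 = 3.551 / 0.10176 = 34.9, so 35
- 35 / (1 − 0.20) = 43.75, so 44 per arm and 88 in total

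This reproduces the stated "assuming a follow-up loss rate of 20%, 88 eligible patients (44 in each group) are needed". Power is 80.1% with 35 per arm. The trial is therefore sized on a between-arm test of proportions, which Statistical methods never clearly assigns to dermatitis incidence.

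**What Friedman detects.** Assumed inputs, not from the documents: 35 per arm, four visits with means 0.5, 1.5, 2.5, 2.5 in both arms, patient SD 1.5, residual SD 1.5, scores rounded and kept within 0 to 10, no treatment effect, 2,000 trials.

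- Friedman within one arm, p < 0.05: 99.95%
- Mann-Whitney between arms at the last visit, p < 0.05: 5.4%

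Friedman responds to time. The between-arm test keeps its nominal level.

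**Pre-post test of dermatitis at the planned rates.** 0.467 × 35 ≈ 16 and 0.786 × 35 ≈ 27 (rounded down). Two-sided Fisher, treating before and after as independent:

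- 0/35 to 16/35: p = 3.3 × 10⁻⁶
- 0/35 to 27/35: p = 2.6 × 10⁻¹²

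Both arms are strongly significant although their rates differ as planned, so the test does not separate them. Starting from zero, p is 0.054 with 5 of 35 affected and 0.025 with 6 of 35.

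**Ignoring the pairing.** Assumed: 35 patients, rate 0.5 at both times, no change, 10,000 trials. The true type I error of an unpaired chi-square test at nominal 5% is:

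| Within-patient correlation | 0 | 0.3 | 0.5 | 0.7 |
|---|---|---|---|---|
| Type I error | 4.1% | 1.4% | 0.5% | 0.01% |

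Power for a true change from 30% to 50% (assumed; 44 patients, 4,000 trials) depends on the assumed latent correlation:

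| Latent correlation | 0 | 0.3 | 0.5 | 0.7 | 0.9 |
|---|---|---|---|---|---|
| Chi-square | 49% | 49% | 49% | 48% | 48% |
| Exact McNemar | 39% | 46% | 55% | 64% | 83% |

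Positive pairing makes the unpaired test conservative. The paired test gains power only from moderate correlation upwards, and loses at low correlation.

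**The case against.** A reader might infer that the plan never tests the cream against control. The documents do not support that. The same section gives log-rank and Cox for dermatitis, so the primary outcome has an unadjusted and an adjusted between-arm analysis. Linear regression covers the VAS, so objective (a), discomfort, is covered too.

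A reader might also take it as settled that chi-square and Fisher will be run on paired data. The sentence structure points that way, but the abstract and the sample size both speak of independent groups, and on that reading these are between-arm tests. Toxicity grade treated as categories would then have a between-arm test, though one that ignores the order of the grades. The text is ambiguous here and needs to be made explicit.

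Repeated-measures ANOVA respects pairing and can carry an arm factor. The named tests are given as examples, and a condensed article may leave model terms to a fuller document. This stands, but it does not help the Friedman branch. How often scores would take that branch is not known from the documents; bounded scores of 0 to 4 and 0 to 10 make it plausible.

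Nor does the protocol propose to read significance in one arm and not in the other as efficacy. The simulations show what the tests respond to; they do not show that the results will be misread.

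**Conclusion.** The point holds as an inconsistency with a specific gap. The step that tests means and proportions is framed as pre-post, against the two-arm superiority design, the abstract and the basis of the sample size. Skindex-29 and toxicity grade have no between-arm test named, and on the non-normal branch they meet a test that cannot compare the arms. Objective (b) is explicitly a comparison between arms and is left without one.

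The size is limited. Two secondary outcomes are affected, the primary outcome keeps its between-arm analyses, and N = 88 is unchanged. The 99.95% and 5.4% rest on assumed score distributions. The Fisher values rest on the planned rates and on no dermatitis at the start; a pre-post test need not be significant at lower rates. The power gain from pairing depends on an undocumented correlation and carries no weight here. This should be fixed before the data are analysed.

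**What to change.** Rewrite the pre-post passage of Statistical methods:

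- State that chi-square or Fisher compares dermatitis proportions between arms, in line with the abstract and the sample size.
- Skindex-29: ANCOVA of the final score on arm and the score taken before radiotherapy. The Interventions section has the radiation oncologist administer the questionnaire at that point, and again has it completed at every follow-up visit, whereas Table 1 shows it only at t1 and t4. Reconcile these so that the baseline is certain.
- Toxicity grade: an ordinal or repeated-measures model that includes arm.
- VAS: include arm and arm-by-visit in any repeated-measures analysis.
- Report within-arm change descriptively only. If a paired test of proportions is kept, use McNemar (two time points) or Cochran Q (more than two).

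The cost is one passage of text and one correction to reconcile Table 1 with Interventions. The analyses use data the protocol already plans to collect, and the sample size does not change.

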**Secondary outcomes**	
Onset and duration of RD	Time of onset and duration of post-radiation dermatitis
Toxicity in patients’ irradiated skin	Common toxicity criteria of the cooperative group for skin suggested by the RTOG Foundation (https://www.rtog.org) [18]
Discomfort and pain concerning symptoms and signs related to dermatitis	Degree of skin discomfort caused by radiation. Subjective assessment and quantification by the patient on an ordinal scale (0 to 10) Pruritus, pain, itching, or peeling of the skin
Quality of life	Quality of life of patients with skin conditions Skindex-29 questionnaire [19]

In addition, secondary outcomes include the level of toxicity in patients’ irradiated skin. It will be assessed according to the common toxicity criteria of the cooperative group for skin suggested by the RTOG Foundation (https://www.rtog.org) [18] according to which toxicity is classified into five levels: 0 for no toxicity or no change; 1 for scattered macular or papular rash or erythema that is asymptomatic; 2 for scattered macular or papular rash or erythema with pruritus or other associated symptoms; 3 for symptomatic generalized macular, papular, or vesicular rash; and 4 for exfoliative dermatitis or ulcerative dermatitis.

The assessment of discomfort and pain concerning symptoms and signs related to dermatitis is based on the subjective assessment and quantification by the patient on an ordinal scale (range 0 to 10), the Visual Analogic Scale (VAS), answering the following question: What score would you rate from 0 (where 0 is the situation where you do not feel symptoms such as pruritus, pain, itching, or peeling of the skin) to 10 (where 10 is the situation where you notice the most symptoms) to your skin problem where do you have the lesion?

Quality of life will be assessed by completing the Skindex-29 questionnaire. Skindex-29 is a self-administered questionnaire to measure the quality of life of patients with skin conditions every 4 weeks, consisting of 29 items. The Spanish version of Skindex-29 has been validated [19].

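### The Shapiro-Wilk switch to Friedman can leave the quality-of-life comparison between arms without a stated test

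*Protocol article*

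**What the plan says.** All of this is in the Protocol article.

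- **Statistical methods, change over visits.** "A pre-post-intervention comparative analysis will then be performed with the endpoints used". For quantitative variables the test is "parametric, such as ANOVA for repeated measures, if the variables follow a normal distribution", with Shapiro-Wilk named as the check, or "non-parametric, such as Friedman’s test, if they do not follow it".
- **Statistical methods, between arms.** "the results will be statistically compared between groups using the log-rank test after estimating the survival curve with the Kaplan-Meier method". Adjusted analyses of the product effect follow: Cox regression for the dermatitis endpoints and, for discomfort, "Multiple linear regression analysis-dependent variable: results obtained with the VAS". Skindex-29 is named in none of these.
- **Outcomes.** "Quality of life will be assessed by completing the Skindex-29 questionnaire"; it is a secondary outcome. Discomfort is a 0-10 ordinal score.
- **Objectives, secondary objective (b).** Quality of life before and after treatment is to be compared between women who are and are not prescribed the cream.
- **Abstract, Methods.** A test for independent means and proportions is mentioned, tied to no outcome or visit.
- **Schedule of Skindex-29.** Interventions has it given before radiotherapy and at each of four follow-up visits. Table 1 marks it at two time points only, the first and last follow-up visits, and not at t=0.

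**The concern.** The method for the quantitative secondary outcomes stays open until a preliminary test has been run on those same outcomes. The two branches also do not answer the same question. Repeated-measures ANOVA can carry arm as a between-patient factor, although the protocol does not say that it will. Friedman ranks each patient's own visits and cannot carry one. A failed normality test can therefore turn an analysis that could compare the arms into one that only asks whether scores moved over time.

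For discomfort, the planned linear regression still addresses the arms. For quality of life, the Statistical methods section offers no substitute. At stake is whether secondary objective (b) is answered by a prespecified comparison, or by one chosen after the data are seen.

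**Working it through.** **1. The plan's own figure.** The protocol states no number for the normality rule. The number it does give, the sample size, sets the n used below. With 46.7% and 78.6%, alpha 0.05 (two-sided assumed), power 0.80 and no continuity correction:

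n = [1.960·√(2·0.6265·0.3735) + 0.842·√(0.467·0.533 + 0.786·0.214)]² / 0.319² = (1.341 + 0.544)² / 0.1018 ≈ 34.9, so 35 per arm.

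35/0.80 = 43.75, so 44 per arm and 88 in total. This reproduces the plan. About 70 patients are expected to be evaluable.

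**2. How often the switch triggers, and whether ANOVA needs it.** Assumptions: four visits, latent AR(1) correlation 0.6, Shapiro-Wilk at 5%, 1,500 runs per cell. ANOVA uses the Greenhouse-Geisser correction; the test is of the visit effect. Results at n=70:

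| Assumed shape | Fails at one visit | Fails at any of 4 | Type I, ANOVA / Friedman | Power, ANOVA / Friedman |
|---|---|---|---|---|
| Normal | 5.3% | 18.7% | 4.6% / 4.8% | 75.5% / 62.1% |
| Integer 0-10, mid-range | 57.2% | 95.8% | 5.0% / 5.7% | 72.9% / 64.6% |
| Integer 0-10, floor | 100% | 100% | 5.1% / 6.3% | 70.1% / 63.0% |
| Strongly skewed | 100% | 100% | 3.9% / 4.3% | 62.1% / 61.7% |

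Over n = 35, 70 and 88, ANOVA type I error was 3.7-6.0% and Friedman 4.0-6.7%. The Monte Carlo standard error at 5% is √(0.05·0.95/1500) = 0.6 points. ANOVA did not need the protection.

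The integer rows resemble the VAS. Skindex-29 may be smoother. With gamma data at 70 patients and correlation 0.5, at least one of four visits failed in 73% of trials at skewness 0.5 and 99.8% at skewness 1.0. With only Table 1's two time points the rates are lower: for normal data about 1 − 0.95² = 9.75% if the visits were independent.

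**3. What Friedman says about treatment.** 35 per arm, both arms worsening over visits, 3,000 runs:

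| Test | No arm difference | 0.6 SD arm difference |
|---|---|---|
| Friedman, arms pooled | significant in about 99% | 99-100% |
| ANOVA with arm as factor, arm effect | about 5% | 85-90% |
| Mann-Whitney on patient means | 4.5-5.6% | 86-88% |

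Pooled Friedman gives the same answer whether or not the cream works. Running it within each arm does not help: it was significant in about 83-89% of runs in either arm, with or without a difference.

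**4. Power of the rule as written.** The last column in step 2 compares always-ANOVA with always-Friedman. The plan's rule is two-stage. Simulated as such (gamma marginals, correlation 0.5, Friedman if any of four visits fails, 0.45 SD shift trend at n=35, rescaled at 44 and 70, 1,500 runs):

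| Skewness | Fixed ANOVA | Two-stage rule |
|---|---|---|
| 0 (normal) | 62-63% | 60-61% |
| 0.5 | – | 1.5-5 points lower |
| 1.0 | 59-61% | 61-62% |
| 1.5 | 58-59% | 77-79% |
| 2.0 | 56-60% | 89-94% |

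Type I error of the two-stage rule was 4.2-6.3%. A separate run gave losses of 1-2 points for normal data and 3-7 for mildly skewed or bounded integer scores, and gains of about 18-36 at skewness 1.5-2.0. The skewed row in step 2 shows no gain because its trend was applied on the latent scale, before the skewing transformation, instead of as a plain shift.

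**The case against.** **The rule is stated in advance and the analyst is blinded**, so there is little discretion. That is fair, and the two-stage rule keeps its type I error. It does not restore a treatment factor to Friedman.

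**The protocol says such as Friedman, and the Abstract mentions a test for independent means.** A between-arm comparison of quality of life may well be intended. But the Abstract's phrase names no outcome or visit, and the Statistical methods section does not carry it through to Skindex-29. The intention is plausible; the test is not stated.

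**A reader might infer a general loss of efficiency.** Friedman's asymptotic efficiency against ANOVA under normality is (3/π)·k/(k+1), which is 0.76 at four visits. That figure belongs to normal data, where the switch seldom triggers. Where it triggers most, the rank test may be level or better. The documents give no distribution, so no general loss can be claimed.

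**A reader might infer that the treatment analysis of discomfort is chosen by the data.** It is not: the adjusted VAS regression carries no normality condition. Nor do the two VAS analyses contradict each other, since change over visits and an adjusted product effect are different questions.

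**A reader might see a conflict with the promised intervals.** "The calculation of the main estimators with their corresponding confidence intervals for 95% safety will also be performed" sits in the descriptive step, and using Friedman does not prevent estimates from being reported.

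**The VAS may have fewer contributors.** Interventions asks only patients with dermatitis to score discomfort, on 1-10 where Outcomes has 0-10. At the planned rates that is about 0.467·35 = 16 and 0.786·35 = 28 patients. A t-test at 16 versus 28 still held 4.8-5.0% type I error (20,000 runs; skewness up to 2, zero-heavy and 1-10 integer scores).

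Whether normality is checked per visit, per arm or on residuals is detail commonly left to an analysis plan, and is not held against the protocol.

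**Conclusion.** The point holds for secondary quantitative outcomes, and chiefly for Skindex-29. The normality switch is unnecessary for validity at this sample size and will often trigger on bounded, integer or skewed scores. Once it triggers, the named analysis cannot compare the arms, and the Statistical methods section supplies no other comparison for quality of life. Secondary objective (b) can then be left without a stated test.

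The power consequence is small and of uncertain sign: about 1-7 points lost for near-normal or bounded scores, and a gain for some strongly skewed ones. The case for change rests on the missing arm comparison, not on efficiency. Discomfort is less exposed. RD incidence and the sample size of 88 are untouched.

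The trigger rates, error rates and power all rest on assumed distributions, correlations and effects. That Friedman has no treatment factor rests on none of them.

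**What to change.** Delete the Shapiro-Wilk switch and fix one between-arm analysis per quantitative outcome, whatever any normality test shows. One suitable form is a linear mixed model with arm, visit and arm-by-visit; another is ANCOVA at the final visit. For quality of life, adjust for baseline Skindex-29. Report the arm difference with its 95% confidence interval. Keep a rank-based between-arm test, such as Mann-Whitney on patient means, as a labelled sensitivity analysis.

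Baseline adjustment relies on the pre-radiotherapy questionnaire described under Interventions. Table 1 shows none at t=0 and only two time points, so the two schedules must be reconciled first.

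The cost is a sentence or two in Statistical methods and no extra data. The small downside is lower power than a rank test if scores prove strongly skewed, which the sensitivity analysis would show. Trial status says the study concluded in June 2023. If the analysis is still to come, record the choice before it is run; otherwise the report should disclose which branch was taken and how the arms were compared.
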